### Compliance

If an intake of folinic acid is forgotten, it should not be administered at the time of the next intake.

Compliance will be assessed retrospectively by counting the number of capsules remaining at the end of treatment. The parents will bring all the blister packs of capsules, whether full or empty, to each consultation for this purpose. If the parents forget to bring the treatment to the consultation, they will be asked to send the blister packs by post.

### Storage and distribution

The treatment will be stored in a safe place, at room temperature or under refrigeration.

A stock-taking form will be completed by the CMJL, in the form of a table. This form will facilitate distribution of the correct treatment to the correct patient and the return of unused medication. At the end of each course of treatment, unused products will be counted for the determination of compliance by the CMJL, before being destroyed.

### Randomisation

Prospective randomisation, based on the use of random number tables, will be applied. Randomisation will be carried out in blocks to prevent imbalance between the two groups. This randomisation will be carried out by an organisation independent of the Centre Médical Jérôme Lejeune.

### Emergency decoding

A set of envelopes making individual decoding possible will be stored at the Centre Médical Jérôme Lejeune. Treatment decoding will be allowed only if knowledge of the treatment administered is liable to modify subsequent treatment. In this trial, there should therefore be no need to open the emergency decoding envelopes.

However, in cases of emergency decoding, the name and signature of the person responsible for the decoding will be noted on the decoding envelope and in the observation notebook, together with the date, time and reason for decoding and action taken as a result. The opened decoding envelope will be placed in the pocket of the observation notebook. The time of decoding will mark the end of the observation period for the subject concerned.

In no case will these envelopes be used for decoding at the end of the trial.

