## trial description and chronology

The total duration of follow-up for any given patient in the trial will be 1 year ± 30 days.

The first medical consultation will include:

- Information about the trial and the signing of the consent form;
- Confirmation of the diagnosis, checking for the presence of karyotyping data in the patient's medical records;
- Checking the inclusion and non-inclusion criteria, including, in particular, ability to undergo the revised Brunet-Lezine test for determining developmental age (DA);
- A general clinical and neurological examination, with measurement of height, weight and CC;
- Prescription of routine biological tests (blood formula, iron, ferritin, thyroid assessment) and other specific examinations, if necessary.

The first consultation with the psychologist will include a psychological examination and the revised Brunet-Lezine test.

Intermediate contact will be made with the parents at intervals of no more than two months. During these intermediate contacts by telephone, the interview by a doctor from the CMJL will focus particularly on the tolerance of folinic acid treatment.

If necessary, the final consultation may take place early, in cases of withdrawal from the study.

The intermediate consultation (6 months ± 15 days) and the final visit (1 year ± 30 days) will include:

- A general clinical and neurological examination, with measurement of height, weight and CC;

- The recording of any adverse events;

- The recording of the doctor's opinion concerning the child (CGI);

- The recording of the overall opinion of the psychologist concerning the development and behaviour of the child on a visual analogue scale (VAS);

- The revised Brunet-Lezine test (determination of DA);

- The recording of the parents' opinion on the treatment of the child;

- The prescription of routine biological tests (blood formula, iron, ferritin, thyroid assessment) and other specific examinations if required.

The entire study will therefore include only standard examinations: three medical examinations, three psychological examinations and three sets of standard biological tests. Between consultations, three to five telephone contacts are planned to help the family and for the monitoring of tolerance and compliance with treatment. If possible, all the examinations will take place on the same day, with the same doctor and the same psychologist.

The total duration of the inclusion period will be 1.5 years.

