## exclusion criteria

Patients will be removed from the study if one of the following criteria is met:

- Occurrence of myeloproliferative syndrome;
- Initiation of thyroid hormone treatment during the study (patients already on stable thyroid extract treatment for more than 3 months may be included);
- Folic or folinic acid treatment (other than that studied) for more than two months during the trial: Alvityl®, Azedavit®, Azinc®, Carencyl®, Cernevit®, Elevit®, Elvorine®, Folinate de calcium, Folinoral®, Forvital®, Léderfoline®, Lofenalac®, Osfolate®, Perfolate®, Plenyl®, Quotivit®, Soluvit®, Spéciafoldine®, Synergyl®, Tardyféron®, Vivamyne®, Zédène®,
- Treatment with a drug with antifolate activity for more than two months of the year (methotrexate, phenytoin).

For patients withdrawing early from the trial, as much information as possible will be obtained by telephone and the final examination will be carried out as soon as possible (within a month of withdrawal).

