# adverse effects

All adverse events occurring during the trial will be described by the investigator in the observation notebook, whether or not they are related to the treatment studied: nature, severity, duration, frequency, reversibility, cessation of treatment. An assessment of the extent to which the event can be attributed to the treatment will be recorded. If treatment is stopped for a minor adverse event or the implication of folinic acid is unclear, a rechallenge test will be carried out, if possible.

Intercurrent illnesses occurring during the trial will be treated as adverse events.

If an adverse event is present at the end of the study, the investigator will transmit reports relating to its progression to the study monitor until this event is cured or stabilised.

Adverse events will be considered serious if they place the subject's life in danger, lead to death, require or prolong hospitalisation or cause disability or significant temporary or permanent clinical incapacity. Serious adverse events will be reported immediately to the monitor (within 24 hours, by telephone) who will declare them to the AFSSaPs. Other adverse events must be notified to the monitor within eight days.

Written confirmation, on a form for recording adverse events, must be sent to the monitor within three days of the occurrence of a serious adverse event.

If a serious or highly unpleasant adverse event is attributed to the treatment studied, the treatment will be stopped and symptomatic treatment initiated.

All new information relating to this research and with implications for patient safety must be declared, in the form of a toxic or unexpected effect declaration, to AFSSaPS, and should be communicated to the investigators.

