# losses to follow-up and premature withdrawal from the trial

The reasons for which a subject may be withdrawn from the trial are as follows:

- Demand from the patient, withdrawal of consent;
- Clear aggravation;
- Occurrence of a serious or unpleasant adverse effect associated with the product tested;
- Poor compliance
- Occurrence of myeloproliferative syndrome;
- Initiation of thyroid hormone treatment during the trial (patients already on thyroid extracts treatment for more than 3 months may be included);
- Treatment with folic or folinic acid (other than the product studied) for more than two months during the trial.

The reasons for the treatment being stopped early or for premature withdrawal from the trial should be documented and reported clearly in the observation notebook, on the appropriate page. All cases of premature cessation of treatment or withdrawal will be analysed in terms of tolerance and efficacy, provided that it is possible to obtain the appropriate data.

The number of subjects lost to follow-up should be minimised and as much information as possible should be collected for these subjects (by postal or telephone contact, for example).

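### The emergency decoding rule ends a child's observation at decoding and is not reconciled with the protocol's rules on adverse-event follow-up, early final examination and missing data

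*Protocol*

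**What the plan says.** The Emergency decoding section (Protocol, Treatments) sets one criterion: "Treatment decoding will be allowed only if knowledge of the treatment administered is liable to modify subsequent treatment". It expects the procedure to go unused: "In this trial, there should therefore be no need to open the emergency decoding envelopes". If an envelope is opened, the person responsible, date, time, reason and resulting action are recorded, and then: "The time of decoding will mark the end of the observation period for the subject concerned". No exception is made for adverse events, laboratory tests or the Brunet-Lezine test.

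Five other sections bear on what happens next:

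- **Adverse effects.** Where an event has not resolved when the study closes, "the investigator will transmit reports relating to its progression to the study monitor until this event is cured or stabilised".
- **Trial description and chronology.** Follow-up is one year ± 30 days. "If necessary, the final consultation may take place early, in cases of withdrawal from the study".
- **Exclusion criteria.** Children who withdraw early are followed by telephone as far as possible and have the final examination within a month of withdrawal.
- **Losses to follow-up and premature withdrawal.** "All cases of premature cessation of treatment or withdrawal will be analysed in terms of tolerance and efficacy", subject to the proviso that the data can be obtained.
- **Missing data.** A child who does not return at one year has the intermediate examination used as the final one. A child with nothing after the initial examination is treated as missing.

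**The concern.** The sentence is a stated rule on data collection, not a detail left for later. It closes observation because of something that happens after randomisation, although the child could still be seen. Since decoding requires that knowledge of the treatment might alter later treatment, decoded children are unlikely to be a random subset, and their number could differ between arms.

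Two things are at stake. Tolerance is a secondary aim, and the Adverse effects section asks for duration and reversibility of every event, which needs continued observation. The principal criterion is the change in developmental age (DAf − DA0), and a literal reading removes the one-year DAf. A statistical analysis plan could say how to handle such a gap, but it cannot recover data that the protocol told the site not to collect.

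**Working it through.** **1. Do the other sections clearly apply to a decoded child?**

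| Section | What it could rescue | Why it does not settle the matter |
|---|---|---|
| Adverse effects | Outcome of an event still present | Refers to the end of the study; does not say whether that includes observation closed by decoding; does not cover events that begin later |
| Trial description; Exclusion criteria | Early final examination and telephone information | Written for withdrawals; decoding is not among the four exclusion criteria |
| Losses to follow-up | Analysis for tolerance and efficacy | Decoding is not among the seven reasons listed; applies only where data can be obtained |
| Missing data | Six-month value used as final | Written for children who do not return, not for those whose observation the protocol closes |

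Some decoded children would qualify by another route, such as an unpleasant adverse effect associated with the product. A child decoded for an event not attributed to the product, or to help choose another treatment, does not clearly qualify.

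**2. What one child loses (illustration: decoding at month 3).**

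- Literal reading: 12 − 3 = 9 months of adverse-event collection, two of three laboratory sets (6 and 12 months), and every post-baseline Brunet-Lezine result.
- If the withdrawal rules apply: an examination by about month 4 supplies one laboratory set and a developmental age, but over roughly 4 months instead of 12.

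**3. Is it a power problem?** Inputs from the number of cases section: means 0.666 and 0.900 years, SD 0.4, two-sided α 0.05, power 80%.

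- Difference = 0.900 − 0.666 = 0.234 years; standardised, 0.234 / 0.4 = 0.585.
- Two-sample t test (noncentral t): 46.85, so 47 per group, with power 80.1%. The protocol's figure is reproduced.
- At 50 per group: 82.5%.
- No decoding rate is given. Assuming all losses fall in one arm:

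| Lost from one arm | Power |
|---|---|
| 1 | 82.2% |
| 3 | 81.3% |
| 5 | 80.4% |
| 6 | 80.0% |
| 7 | 79.5% |

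A few decodings barely affect power.

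**4. How far could the estimate move?** Assume decoding after the six-month visit, the missing-data rule applied, and roughly linear development over the year. The carried-forward gain is then half the yearly gain, and the understatement is the other half:

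- placebo: 0.666 / 2 = 0.333 years
- folinic acid: 0.900 / 2 = 0.450 years

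For that child, either figure exceeds the whole planned difference of 0.234. With an assumed three such children in one arm of 50, the arm mean shifts by:

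- placebo: 3 × 0.333 / 50 = 0.020 years, or 0.020 / 0.234 ≈ 9% of the planned difference
- folinic acid: 3 × 0.450 / 50 = 0.027 years, or 0.027 / 0.234 ≈ 12%

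The shift narrows the difference if the children are on folinic acid and widens it if they are on placebo. For children decoded before six months, with no early examination, the bias cannot be computed because there is no outcome.

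**The case against.** The strongest reply is that the sections fit together. Once observation ends, ongoing events are reported until resolved; the early final examination can be read as covering anyone who leaves early, since it is not expressly confined to the listed criteria; and the missing-data rule handles the rest. No decodings are expected. On this view the gap is an unstated link, not a contradiction, and full visits after unblinding are one design preference among several.

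Much of this stands. The joint reading is workable and the practical effect is probably small. What remains is that the protocol does not say the joint reading is intended. Even on that reading, new adverse events and the one-year assessment on schedule are not provided for.

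Three stronger conclusions might be inferred, and the documents do not support them:

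- **Safety follow-up stops altogether.** The Adverse effects section may still cover an ongoing event, so follow-up is not assured rather than abolished.
- **The children affected are exactly those with the most serious events.** The criterion is possible modification of treatment; seriousness is not mentioned. The protocol also provides for stopping treatment after a serious attributed event without mentioning decoding.
- **Three decodings in one arm would exhaust the sample-size margin.** That arm would fall to 47, but with 50 in the other arm power is still 81.3%. It reaches about 80% only at six losses.

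**Conclusion.** The point holds as an unreconciled rule that can cause avoidable and possibly informative loss of tolerance and outcome data. It is not a power problem, and it is not proof that safety follow-up is abandoned. For an individual child the loss can be large: up to 9 of 12 months and the primary outcome in the month-3 illustration. For the trial it is probably small: about 9–12% of the planned difference with three children carried forward in one arm. That range rests on an assumed number of decodings and on linear development; the protocol gives no decoding rate. The rule should be changed because the correction is cheap and an emergency procedure has to be clear when the unexpected happens.

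**What to change.** Replace the sentence that closes observation with wording to this effect:

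- The decoding is recorded as already required, and the child is flagged as unblinded.
- Whether or not study treatment continues, adverse-event follow-up, telephone contacts and the scheduled six- and twelve-month assessments, including laboratory tests and the Brunet-Lezine test, continue with parental agreement.
- The child stays in the analysis.
- Where possible, the psychologist is kept unaware of the allocation. Any Brunet-Lezine result, CGI, VAS or parental opinion obtained with allocation known is identified as unblinded. The flag must include the Brunet-Lezine test, since it is the primary measure and the envelopes are held at the same centre.

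Then align the exclusion criteria, Adverse effects, missing data and losses to follow-up sections. They should say whether decoding counts as withdrawal, whether the end of the study includes an individual child's end of observation, and when the six-month value may be carried forward.

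The cost is one replaced sentence, a few cross-references and the amendment procedure. The visits are already in the schedule. The downside is that a few later ratings may be made with allocation known; because they are flagged, they can be examined separately.

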## associated treatments

Other treatments will be avoided during the study. However, if necessary, they will be authorised and noted in the observation notebook, except for treatments with folic or folinic acid (other than the product studied) for more than two months during the trial, which will lead to exclusion from the trial.

# adverse effects

All adverse events occurring during the trial will be described by the investigator in the observation notebook, whether or not they are related to the treatment studied: nature, severity, duration, frequency, reversibility, cessation of treatment. An assessment of the extent to which the event can be attributed to the treatment will be recorded. If treatment is stopped for a minor adverse event or the implication of folinic acid is unclear, a rechallenge test will be carried out, if possible.

Intercurrent illnesses occurring during the trial will be treated as adverse events.

If an adverse event is present at the end of the study, the investigator will transmit reports relating to its progression to the study monitor until this event is cured or stabilised.

Adverse events will be considered serious if they place the subject's life in danger, lead to death, require or prolong hospitalisation or cause disability or significant temporary or permanent clinical incapacity. Serious adverse events will be reported immediately to the monitor (within 24 hours, by telephone) who will declare them to the AFSSaPs. Other adverse events must be notified to the monitor within eight days.

Written confirmation, on a form for recording adverse events, must be sent to the monitor within three days of the occurrence of a serious adverse event.

If a serious or highly unpleasant adverse event is attributed to the treatment studied, the treatment will be stopped and symptomatic treatment initiated.

All new information relating to this research and with implications for patient safety must be declared, in the form of a toxic or unexpected effect declaration, to AFSSaPS, and should be communicated to the investigators.

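### Once treatment is stopped for a serious or highly unpleasant event of unclear cause, the protocol's written default is rechallenge, except for myeloproliferative syndrome

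*Protocol*

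**What the plan says.** The section on adverse effects of the protocol contains two rules on what follows an event.

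- **Rechallenge.** When "treatment is stopped for a minor adverse event or the implication of folinic acid is unclear, a rechallenge test will be carried out, if possible".
- **Stop.** "If a serious or highly unpleasant adverse event is attributed to the treatment studied, the treatment will be stopped and symptomatic treatment initiated".

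The same section defines a serious event. Besides danger to life and death, the definition covers events that "require or prolong hospitalisation or cause disability or significant temporary or permanent clinical incapacity". On reporting it states: "Serious adverse events will be reported immediately to the monitor (within 24 hours, by telephone) who will declare them to the AFSSaPs". It also states: "Intercurrent illnesses occurring during the trial will be treated as adverse events".

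The section on losses to follow-up and premature withdrawal opens its list with "The reasons for which a subject may be withdrawn from the trial are as follows". Among the seven reasons are "Clear aggravation" and "Occurrence of a serious or unpleasant adverse effect associated with the product tested".

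Three other sections bear on the point. The exclusion criteria require removal on four listed grounds, one of them myeloproliferative syndrome. The section on dose and duration lets the investigator lower the dose, or stop early, for functional problems such as irritability. The section on emergency decoding permits unblinding only where it could change later treatment, and expects that it will not be needed.

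**The concern.** The rechallenge sentence joins two conditions with *or*. Read as written, *minor* belongs to the first, and the second stands alone. The protocol has a definition of *serious* in the same section but does not use it to limit rechallenge.

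The children are included at about 6 to 24 months of age. If one of them has a life-threatening, hospitalising or disabling event, dosing is stopped, and nobody can say whether the product was responsible, the text points toward giving it again. The cautious default would be the reverse: no re-exposure until another cause has been established. Here someone has to use discretion to depart from the default in order to protect the child.

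Unclear causality is a realistic category in this trial. Causality is normally judged blind, and intercurrent illnesses count as adverse events, so an illness leading to admission is serious by definition.

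**Working it through.** No arithmetic applies. The check sorts events by severity and causality and asks which rule governs each.

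1. **Minor event, treatment stopped.** The first condition of the rechallenge sentence applies. Rechallenge is the default, and this is unobjectionable.
2. **Serious or highly unpleasant event, attributed to treatment.** The stop rule applies and treatment ends.
3. **Myeloproliferative syndrome, any cause.** The exclusion criteria make removal mandatory, so re-exposure is in effect barred.
4. **Any other serious or highly unpleasant event of unclear cause, treatment stopped.** The stop rule does not reach it, because there is no attribution. The second condition of the rechallenge sentence does. The written default is rechallenge.

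Case 4 is the gap. Each remaining safeguard was then tested for whether it closes it:

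- **The closing words of the rechallenge sentence.** They leave room for judgement but prohibit nothing.
- **Withdrawal list.** It is permissive. Of its seven reasons, one names a serious adverse effect, and that one requires association with the product. Clear aggravation and a request to withdraw need no attribution, but they allow withdrawal without forbidding rechallenge.
- **Exclusion criteria.** Of the four grounds, only myeloproliferative syndrome is itself a serious medical event. There is no general criterion for serious events.
- **Dose and duration.** Early stopping is at the investigator's discretion and is written for functional problems, which may or may not be serious. Nothing is said about restarting.
- **Reporting within 24 hours.** This is notification. The sentence gives the monitor no power to stop or bar dosing.
- **Emergency decoding.** It is allowed where it could change treatment, and it ends the child's observation period. It is neither required nor expected.

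None of these bars rechallenge in case 4.

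An illustration from the document, with no rate claimed: current infantile seizures prevent entry under the non-inclusion criteria, but seizures arising during the trial are not among the exclusion criteria (only phenytoin for more than two months is). If a child were admitted with new seizures, dosing were stopped and the cause stayed unclear, the default would be rechallenge, although the same condition would have prevented entry.

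**Size.** The planned allocation is 50 on folinic acid and 50 on placebo, so at most 50 children could be re-exposed to the drug itself. The document gives no rate of serious events, admissions or treatment stops in this age group, so no expected number can be derived.

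**The case against.** The strongest reply is that the sentence operates only after a stop, and no rule requires a stop for a serious event of unclear cause. Someone has already used judgement to stop, and the closing words leave judgement over restarting. This stands as a limit on the point: rechallenge is a default, not a duty. It does not remove the default.

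A second reply is that the text appears to be a translation, and its authors may have meant *minor* to cover both conditions, contrasting minor or doubtful events with serious attributed ones. That is possible. The sentence does not say so, and if that was the intent, the amendment only makes it explicit.

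A third reply points to context: tolerance is assessed case by case, the dose can be lowered one capsule at a time, the trial is bound to good clinical practice and to operating procedures not shown here, and folinic acid is described as non-toxic. These reduce the weight of the point. But the protocol makes tolerance in this population a secondary aim and asks for monitoring, so it should not assume the answer.

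A reader might infer that the protocol calls for re-exposure after any serious event. It does not: attributed events lead to a stop, and myeloproliferative syndrome leads to removal. A reader might also infer bias in the comparison of developmental age. Nothing in the documents supports that.

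**Conclusion.** The point holds in a narrow form. For a child whose treatment has been stopped for a serious or highly unpleasant event of unclear cause, other than myeloproliferative syndrome, the written default is rechallenge where possible, and no other provision forbids it.

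This rests on reading *minor* as limiting only the first condition, which is what the wording says, and on there being no contrary rule in the operating procedures manual, which cannot be seen. It is a weakness in a safety rule with no effect on sample size, power or the primary comparison. The number of children concerned cannot be estimated and is probably small. It is worth considering because the correction is cheap.

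**What to change.** Replace the rechallenge sentence in the section on adverse effects with text to this effect:

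> If dosing is stopped because of an adverse event that is neither serious (as defined in this section) nor highly unpleasant, and the event is minor or its relation to folinic acid is unclear, rechallenge will be performed where possible. There will be no rechallenge after a serious or highly unpleasant event that is attributed to the treatment or of unclear relation to it. After such an event, treatment may resume only if the investigator records that another cause explains it.

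The threshold covers highly unpleasant events as well as serious ones because the existing stop rule treats the two alike. The last sentence prevents a precautionary pause, for example during admission for an ordinary infection, from becoming a permanent stop once the infection is recorded as the cause. The stop rule and the exclusion criteria stay as they are, and a child whose dosing was never stopped is unaffected.

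The cost is one wording amendment handled through the IRB, with no extra patients, visits or procedures. The downside is that a few children with such events may lose some treatment exposure; the document does not allow their number to be estimated. Their outcome data need not be lost, since the section on premature withdrawal has all early cessations analysed for tolerance and efficacy where data can be obtained.
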